### Statistical analysis

No interim analysis will be performed. Analysis will be based on the intention-to-treat principle. The analysis will be done at the resident level.

For the primary outcome measure, i.e. the proportion of residents with at least one antipsychotic prescription after 12 months, proportions will be compared between the intervention group and control group, using a two-sided cluster-adjusted *χ*^2^-test at a level of significance of α = 0.05 [57]. Corresponding cluster-adjusted 95 % confidence intervals will be calculated. Furthermore, to investigate the time course of the intervention effect, including all the residents observed after 3, 6, 9, or 12 months, drug prescriptions of antipsychotics per resident after 3, 6, 9, and 12 months will be analysed as a dependent variable in a generalised linear mixed (logistic) model with the intervention as a fixed effect, clusters as a random effect, and using covariance patterns to adjust for repeated measurement. This will be done as a secondary analysis.

For the secondary outcome measures, linear mixed models or generalised linear mixed methods will be used, adjusting for clusters by random effects. Subgroup analyses using linear mixed models will be performed for gender and cognitive status. The analysis of all secondary outcomes is interpreted exploratively and not confirmatively.

A detailed description of the statistical analysis can be found in Additional file 2.

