### Cluster-randomisation

The randomisation will be carried out on a cluster level. The randomisation list will be computer-generated by an independent external biometrician, who will be blinded to the identity of the participating organisations and residents. Nursing homes will be allocated to the intervention or control group using a balanced block randomisation, stratified by the three regions Halle (Saale), Lübeck, and Witten as well as the time point of the recruiting phase. Because of the low number of homes per stratum (*n* = 4), no further blocks within the strata are planned. This randomisation list will contain pseudonymous identification numbers for nursing homes and allocation of group A or B.

Parallel to this, responsible coordinators of the three study centres will independently determine and document the allocation (intervention group or control group) for group A and group B at study begin, without informing the external biometrician.

After completion of the baseline measurement of the corresponding recruiting phase, an independent person from the study centre in Lübeck will electronically (password-protected, encoded https portal) assign the randomisation list and nursing home data for concealed allocation [44] and will inform the nursing homes in written form. After confirmation of group allocation by the nursing homes, the assigning person will inform the coordinator of the respective study centre about the allocation results.

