### Measures

#### Institutional level

The description of the participating nursing homes, data on general characteristics, staff characteristics, characteristics of living environment, and living and care concept according to Palm et al. [45] will be gathered from the nursing home director before randomisation. The proportion of eligible residents receiving an antipsychotic prescription will be recorded at baseline and after 12 months.

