### Sample size calculation

The primary endpoint of the study is the proportion of residents with at least one antipsychotic prescription after 12 months (t_4_). The following sample size estimation was performed as described in Donner & Klar [57] for the cluster-adjusted *χ*^2^-test. Based on recent prevalence data, we expect a baseline prevalence of antipsychotic prescription of 30 % [2]. Due to the measures of optimised usual care in the control group and based on the study by Fossey et al. [35], we expect the prevalence in the control group to decline slightly to 26 % after 12 months. We expect a relative risk reduction of approximately 50 % regarding antipsychotic prescription in the intervention group.

Assuming a significance level of 5 % (α = 0.05), a two-sided test for proportions, and an intra-class correlation coefficient (ICCC) of 0.05, an average cluster size of 65 nursing home residents, 15 clusters are required per group to detect a 12 % difference in proportions from 26 % of the control group at 12 months with 90 % power (β = 0.10). Presuming that six nursing homes might drop out, 36 clusters with a total of 2340 residents will be needed.

We expect 25 % of residents with early study termination due to death or moving; the other 75 % of residents of the baseline population we expect to be still living in the nursing home and to be available for the 12-month follow-up assessment. As the outcome, the analyses will focus on the group of residents living in the nursing homes after 12 months. Assuming that new residents will all be willing to participate in the study, this will not affect the sample size.

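### The primary chi-square test uses neither each home's pre-randomisation antipsychotic prevalence nor the randomisation strata, so it gives up precision and leaves chance baseline imbalance unadjusted

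*Protocol article*

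**What the plan says.** **Primary test.** In Statistical analysis, for the primary outcome, "proportions will be compared between the intervention group and control group, using a two-sided cluster-adjusted" chi-square test at the 5 % level, with matching cluster-adjusted confidence intervals. No covariate or stratum is named. The secondary model for the time course starts at month 3 and states only intervention (fixed), cluster (random) and a covariance pattern for repeated measures.

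**Randomisation.** Under Cluster-randomisation, allocation is stratified by three regions "as well as the time point of the recruiting phase", with four homes per stratum. For 36 homes that means 36 / 4 = 9 strata. Allocation is released only after the baseline measurement of the phase is complete.

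**Baseline outcome.** Under Institutional level: "The proportion of eligible residents receiving an antipsychotic prescription will be recorded at baseline and after 12 months".

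**Sizing.** Sample size calculation uses the same unadjusted test: "15 clusters are required per group to detect a 12 % difference in proportions from 26 % of the control group at 12 months", with 90 % power.

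**Elsewhere.** Statistical analysis refers details to Additional file 2, which is not shown. Blinding allows the analysis procedure to be adapted after a blinded data review, but names no adjustment.

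**The concern.** A home's prescribing rate before randomisation is a natural predictor of its rate a year later. The protocol expects 75 % of the baseline residents to be still there at 12 months. The value is collected for every home and cannot be affected by allocation, yet the confirmatory test leaves it out.

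The strata raise a related matter. If prescribing differs by region or phase, stratification makes the arms more alike than the test's variance assumes, and the test becomes conservative.

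Two things are at stake. One is precision in the only confirmatory comparison. The other is how the result reads if the arms happen to differ at baseline: part of that difference carries into the estimated effect, and no stated analysis removes it.

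**Working it through.** **Inputs from Sample size calculation.** Two-sided 5 % test, 90 % power, 26 % versus 14 %, "intra-class correlation coefficient (ICCC) of 0.05", "an average cluster size of 65 nursing home residents", 15 homes per arm needed and 18 randomised. For baseline, "we expect a baseline prevalence of antipsychotic prescription of 30" %.

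**Not in the document, so assumed.** The correlation r between a home's observed baseline and 12-month prevalence (0.3 to 0.7), and the share of between-home variance due to strata (0 to 0.4).

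**1. The plan's own figure.** The two-proportion formula gives 232 residents per arm without clustering. The design effect is 1 + (65 − 1) × 0.05 = 4.2. Then 232 × 4.2 / 65 = 14.99, so 15 homes per arm, as stated. The unpooled-variance form gives 228.2 × 4.2 / 65 = 14.75, also 15. Power is 0.901 with 15 homes per arm and 0.945 with 18.

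**2. Chance imbalance at baseline, ignoring stratification.** The variance of one home's proportion is 0.30 × 0.70 × 4.2 / 65 = 0.01357.
- 18 per arm: SD of the arm difference = √(2 × 0.01357 / 18) = 0.0388, or 3.9 points. The 95 % range is ±7.6 points, and the chance of more than 5 points is about 20 %.
- 15 per arm: √(2 × 0.01357 / 15) = 0.0425, or 4.3 points. The 95 % range is ±8.3 points, and the chance is about 24 %.

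**3. How much of an imbalance carries over.** With no effect and both arms at 26 %, the expected shift is the imbalance × r × √(0.26 × 0.74) / √(0.30 × 0.70) = imbalance × r × 0.957. A 5-point imbalance then shifts the estimate by about 1.4, 2.4 or 3.3 points at r = 0.3, 0.5 or 0.7.

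**4. Power for 12 points with baseline adjustment.** The effective n per arm with 15 homes is 15 × 65 / 4.2 = 232.1, divided by (1 − r²). The homes needed for 90 % are 14.75 × (1 − r²). Degrees of freedom spent are ignored here.

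| r (assumed) | Effective n, 15 per arm | Power, 15 per arm | Power, 18 per arm | Homes per arm for 90 % |
|---|---|---|---|---|
| 0 | 232.1 | 0.901 | 0.945 | 14.7 |
| 0.3 | 255.1 | 0.926 | 0.962 | 13.4 |
| 0.5 | 309.5 | 0.963 | 0.984 | 11.1 |
| 0.7 | 455.2 | 0.995 | 0.999 | 7.5 |

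**5. Simulation with strata.** Nine strata of four homes (2:2), 65 residents per home, ICC 0.05, 2500 to 4000 runs per scenario. The planned test is compared with a home-level regression on arm, nine stratum indicators and home baseline prevalence. Here ρ is the correlation of the underlying home effects beyond the stratum. Cells read planned / adjusted.

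| Strata share | ρ | Type I error | Power, 12 points | Power, 8 points |
|---|---|---|---|---|
| 0 | 0.5 | 0.059 / 0.051 | 0.944 / 0.954 | 0.637 / 0.646 |
| 0 | 0.8 | 0.059 / 0.054 | 0.946 / 0.989 | 0.626 / 0.789 |
| 0.2 | 0.5 | 0.042 / 0.050 | 0.959 / 0.976 | 0.640 / 0.706 |
| 0.2 | 0.8 | 0.041 / 0.054 | 0.959 / 0.994 | 0.645 / 0.823 |
| 0.4 | 0.5 | 0.026 / 0.050 | 0.972 / 0.989 | 0.664 / 0.792 |
| 0.4 | 0.8 | 0.023 / 0.044 | 0.970 / 0.997 | 0.661 / 0.858 |

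The planned test is close to nominal when strata do not matter and conservative when they do. Stratification also lowers the chance of a baseline imbalance above 5 points, to 11–16 % at strata shares of 0.2 to 0.4. Under no effect, among trials with such an imbalance, the planned test rejects in 6–16 % and the adjusted one in about 4–7 %.

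Stratum indicators without baseline prevalence change power at 8 points from 0.63–0.64 to 0.59 if strata explain nothing, and from 0.66 to about 0.75 at a share of 0.4. The region-plus-phase main-effects model recommended below was not itself simulated.

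**The case against.** The strongest reply is that nothing here is an error. Test and sample size use the same named method, the 15 homes reproduce, and 36 homes give about 94 % power at the planned effect if none drops out. An unadjusted test is transparent, and random imbalance is already covered by its confidence interval. All of that stands. It does not answer the efficiency point, nor the reading of a trial in which an imbalance is actually seen: coverage holds on average over randomisations, not given that imbalance.

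It is also fair that the gain rests on an unknown correlation. Resident turnover of about 25 %, and medication review and physician education in both arms, could weaken it. At 12 points and low correlation the gain is small.

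Three stronger readings are tempting but not supported:
- A reader might infer that ignoring the strata always costs power. It does not: if strata are not prognostic, adjusting for all nine slightly lowers power.
- A reader might infer that a baseline difference passes in full into the effect estimate. It passes in proportion to the correlation (step 3).
- A reader might infer that the aim of generalising across regions has no regional analysis at all. The article cannot show this. Additional file 2 is not at hand, and Trial objective gives the process evaluation a focus on regional differences.

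Additional file 2 could also hold an adjusted sensitivity analysis. The article nevertheless names the primary test. The first step of the blinded review has neither home identifiers nor allocation, so it cannot reveal an imbalance between arms.

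**Conclusion.** The point holds as a matter of precision and of protection against chance imbalance. The planned test is neither invalid nor underpowered for 12 points.

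Baseline arm differences of several points are to be expected: SD about 3.9 points with 18 homes per arm at 30 % prevalence, ICC 0.05 and 65 residents per home, before the reduction that stratification brings. For the planned effect with 15 homes per arm, power moves from 0.90 to between about 0.93 and 0.995 over the assumed r of 0.3 to 0.7. The gain is generally larger if the true effect is smaller: at 8 points with 18 homes per arm, simulated power is 0.63–0.66 as planned and 0.65–0.86 adjusted. Both ranges rest on assumptions the document does not supply; the direction is secure only as far as baseline prevalence or the strata are prognostic.

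**What to change.** Pre-specify one adjusted primary analysis: either a home-level ANCOVA, or a resident-level mixed logistic model or GEE with a small-sample correction. Include arm, the home's baseline antipsychotic prevalence, and region and recruiting phase as main effects. Use the home-level baseline value, because residents admitted during follow-up have no pre-randomisation value of their own. Report the marginal risk difference with its 95 % confidence interval, and keep the cluster-adjusted chi-square test as a sensitivity analysis. Settle this before allocation is attached to the data.

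The cost is wording, slightly more analysis work and a few degrees of freedom; no new data are needed. With three regions and three phases, main effects use 2 + 2 = 4 degrees of freedom against 8 for nine stratum indicators, plus 1 for baseline prevalence. If strata turn out not to be prognostic, those degrees of freedom can slightly lower power, which is the reason to prefer main effects.

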### Data management

Study data will be recorded, pseudonymised in paper form in the nursing homes, and electronically stored afterwards. The personal data of the study participants (name, birthday, etc.) will be kept separately from the study data. All participating nursing homes will also receive a pseudonymous identification number. Key lists will be stored separately from the study data and will be deleted after final validation of the analytical data set and data freezing.

Data will be entered electronically at the study centre in Lübeck. The data matrix will be based on the codebook created prior to the study. The questionnaires will be read electronically by a scanner-based software (TeleForm®). During scanning and electronic recording, a plausibility check will be performed. Written requests will follow in the case of unclear data or lack of data. Unclearly placed check marks and text fields will be checked and corrected manually. To ensure data quality, important data (e.g. antipsychotic prescription) will be checked by hand. Changes and corrections to the database will be clearly documented. After data freezing, no further data changes will be possible. Data entry will be performed within 1 month after recording.

### Quality assurance

The study will be planned, implemented, and evaluated in accordance with the principles of good clinical practice (ICH-GCP) [58] and the Declaration of Helsinki [59].

A concordant study procedure in all three study centres will be ensured by a central external audit. Data monitoring will increase the credibility of the study and help to improve data collection and archiving procedures. It will be carried out according to a data-monitoring manual which follows GCP and which has been developed and applied in a former study [60].

### Dissemination policy

We plan to publish the study results in a peer-reviewed, Medline-listed journal. All results will be reported referring to this study protocol and to the CONSORT statement extended to cluster-randomised trials [61] as well as to CReDECI [62].

We will set up a German-language homepage for reporting the study results and accessing all materials, including the intervention programme, after the end of trial.

### Ethical and legal considerations

This project has received ethical approval from the ethics committee of the Medical Faculty, Martin Luther University Halle-Wittenberg, Germany (no. 2014–101), as well as from the ethics committees of the Universities of Lübeck (no. 14–239) and Witten/Herdecke (no. 133/2014). All ethics committees will be informed immediately about any protocol amendments and serious or unexpected adverse events as well as a premature end of the study.

## Discussion

Based on previous study results [2, 35], we do not expect any risks for the participating residents. The intervention programme has been tested successfully in the United Kingdom, and the discontinuation of antipsychotics showed no negative consequences [35]. Systematic reviews support only a short-term antipsychotic treatment, because of the significant adverse effects and a lack of evidence for prolonged prescription [17, 31]. We expect that the intervention programme will reduce the current high prescription rate of antipsychotics in nursing homes.

### Trial status

The pilot phase of the study has been started.

## Abbreviations

BPSD: Behavioural and psychological symptoms of dementia
CMAI: Cohen-Mansfield Agitation Inventory
CME: Continuing medical education
CRF: Case report form
DSS: Dementia Screening Scale
EPA: Experts for person-centred care for the elderly
EPCentCare: Effect of person-centred care on antipsychotic drug use in nursing homes (acronym of the study)
GP: General practitioner
ICCC: Intra-class correlation coefficient
ICER: Incremental cost-effectiveness ratio
ICH-GCP: International Conference on Harmonisation—good clinical practice
PCC: Person-centred care
PRN: Pro re nata (“when required”)
QoL: Quality of life
QoL-AD: Quality of life in Alzheimer’s disease
